#### Direct non-medical costs

The direct non-medical costs include the cost of transportation, accommodation, and meals when visiting a physician, the cost of nourishment and healthcare equipment in the patient’s daily life, and formal care fees. The cost of daily nourishment, such as calcium, vitamin, protein powder, and fish oil supplements, include the number of times items were purchased and the amount spent in the last 12 months. The cost of healthcare equipment refers to supplies, such as positioning watches, bracelets, and wheelchairs, used in the last 12 months. Formal care costs are defined as the cost of nursing care given by professional caregivers for patients in nursing homes/gerocomiums/care facilities or at home, including the number of hours of care and the average monthly expenses [27].

#### Indirect costs

Indirect costs include monetary loss caused by the patients’ inability to work, reduction of informal caregivers’ income, treatment of the mental suffering of caregivers, and treatment of unexpected injuries in AD patients or their caregivers. Because the AD patients in this study are aged ≥ 60 years, most of whom are retired as per China’s national regulations, their major source of income is retirement pensions. Therefore, the decrease in a patients’ income is not considered, because it is independent of patients’ health status. Informal caregivers are mostly the relatives or unpaid nonrelatives of patients with no agency affiliation [28]. Investigation of the informal caregivers include the length of time (hours) provided by informal caregivers; the relationship between the caregivers and AD patients; sex, age, and monthly job losses for employed subjects (hours); and monthly salary. Cost for the treatment of mental suffering of caregivers refers to any symptoms triggered or worsened by taking care of AD patients over the past 12 months. The monetary loss caused by injuries to AD patients includes outpatient, examination, medication, transportation, and accommodation costs.

#### Others

To understand the relationship between AD costs and other factors, parameters such as social demographics and disease details are also investigated. The social demographics include sex, age, education level, marital status, occupation, salary, and the number of children. The disease details include age at onset of AD, clinical evaluations (based on ADL, GDS, MMSE and neuropsychiatric inventory [NPI] [29]), and comorbidities (e.g., stroke, diabetes, heart disease, hypertension, hyperlipidemia, lung diseases, cancer, arthritis, and other diseases of the nervous system).

### Data collection procedure

Electronic medical record systems are being used to identify elderly patients diagnosed with AD among outpatients (in the last 3 months), inpatients (in the last 12 months), those living in urban residences and rural residences with their families, and residents of nursing homes, gerocomiums, or care facilities. The diagnosis of AD is re-confirmed by dementia specialists before the start of the study. The intensive dementia training program conducted in national and regional centres included both theory and practice. It comprised the study methods, assessment of the scales and internationally accepted diagnostic criteria of dementia and its subtypes, neuroimaging (CT and MRI), and standard procedures for diagnosis. Investigators are contacting patients and re-confirm the accuracy of the AD diagnosis according to the inclusion and exclusion criteria. Neuroimaging and laboratory tests will be performed when necessary. New patients are also being enrolled during the study period. Face-to-face questionnaires will be administered to AD patients and their caregivers when the data and information could not be collected through electronic medical record or residence health systems. The surveys are being administered by investigators to ensure the accuracy of the diagnosis and data.

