#### Direct medical costs

The direct medical costs include outpatient costs, hospitalisation costs, and out-of-pocket expenses for healthcare medications. Outpatient costs include the reason for the visit (due to AD, AD-related symptoms, or comorbidities), the number of outpatient visits in the past 3 months, and the cost of the last clinic visit in the same 3-months period. The cost of clinic visits includes registration (general physicians or specialists), diagnostic procedures (e.g., consultation, scale evaluation), imaging (e.g., CT, MRI, SPECT, and PET), laboratory tests, medication, and non-drug treatment (such as rehabilitation treatment). The outpatient medication costs are divided into three categories: anti-dementia drugs, medications for the treatment of AD-related symptoms (e.g., sleep disorders, psychiatric symptoms, and gastrointestinal symptoms caused by medications), and the treatment of comorbidities. For anti-dementia drugs the specific medications used and their corresponding costs are also investigated. For comorbidity-associated costs, the types of comorbidity and the associated costs are recorded. Investigations into the cost of hospitalisation included the reason for hospitalisation (AD, AD-related symptoms, or comorbidities), how many times a patient was hospitalised in the past 12 months, and expenditures on the last hospitalisation within the past 12 months. The hospitalisation expenditure includes the cost of the ward bed, formal care, examinations, laboratory tests, treatment (such as rehabilitation, massage, and others), and medications. The term “self-bought medications” means that the patient or their caregivers purchased the medications outside the hospital (out-of-pocket spending). Questions include how many times medications were purchased in the past month and the total expenditure during the same period. The above data also include information regarding the patients’ payment method (including medical insurance for urban workers or town residents, rural cooperative medical insurance, commercial insurance and self-funded) and any out-of-pocket expenses.

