### Measures

#### Total cost per patient per year

The total cost per patient per year is determined by adding the annual direct medical costs, direct non-medical costs, and indirect costs for each patient. When calculating the cost of the recuperation fee for patients who required nursing care in nursing homes, gerocomiums, or care facilities, 8% of the basic cost is subtracted to reflect the AD patient’s basic cost of living [30]. Two approaches are being used to estimate the monetary loss of informal caregivers. For the informal caregivers who have no stable job before taking care of the AD patients, the average labour market income reported by each research centre is being multiplied by the amount of time spent being a caregiver to obtain the monetary loss. For individuals with a stable job before taking care of the AD patient, the monetary loss is being obtained by multiplying the hourly salary before they stop working by the time spent (hours) being a caregiver. All of the costs will be converted into the average annual cost.

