#### Current total number of patients with AD in China

A model is established to estimate the total number of Chinese patients with AD in 2015 based on the literature. The total number of patients with AD is defined as M and the percentage of AD patients who received anti-dementia treatment is defined as d%. Therefore, the number of anti-dementia treated patients (M_1_) is M × d%, and the number of patients not treated for dementia (M_2_) is M × (1–d)%. Based on previous reports, the percentage of AD patients who are treated for dementia is 10–30% [31, 32]. Epidemiological studies have revealed that the number of AD patients in China aged ≥ 60 years in 1990, 2000, and 2010 was 1.93 million, 3.71 million, and 5.69 million, respectively [8, 33, 34]. A linear regression model is used to estimate the age-specific prevalence of AD in 2015 by recording the prevalence of AD among different-aged patients. By multiplying the percentage of AD among elderly individuals aged ≥ 60 years by the total national elderly population (aged ≥ 60 years) in 2015, we obtain the estimated total number of AD patients of China, which is defined as M.

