#### Per capita annual cost of AD patients (who accepted or did not accept treatment)

The cost associated with treating dementia patients (F_1_) is divided into two groups: “outpatient costs” and “hospitalised or inpatient costs.” F_1_1_ is defined as the average annual cost in the inpatient group (average annual cost × the number of inpatients annually), and F_1_2_ is the average annual cost in the outpatient group (average annual cost × the number of outpatients annually). Patients described as not accepting treatment are those who did not select either “outpatient service costs” or “hospitalised costs” in their questionnaire. F_2_ is defined as the average annual cost per AD patient who did not accept treatment.

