#### Nationwide cost due to AD

A pilot study is performed, which reveal that the average annual ratio of inpatients to outpatients in different hospitals is ~1:6. Hence, the number of patients who undergo treatment nationwide (M_1_) is multiplied by 1/7 or 6/7 to obtain the number of hospitalised patients with AD (M_1_1_) and the number of outpatients with AD (M_1_2_), respectively. Thus, the total national annual cost of patients who accept treatment is M_1_1_ × F_1_1_ + M_1_2_ × F_1_2_. M_2_ is defined as the number of patients who did not accept treatment, and this value is multiplied by F_2_ to obtain the total annual national cost of patients who do not accept treatment. Therefore, the total annual national cost of patients with AD is M_1_1_ x F_1_1_ + M_1_2_ x F_1_2_ + M_2_ x F_2_. To estimate the costs attributable to AD, generalised linear models (GLMs) related to coexisting conditions (stroke, diabetes, heart disease, hypertension, lung disease, cancer, arthritis, and psychiatric problems) and demographics (sex, age, educational level, marital status, and household income) are used. Moreover, we estimate the total numbers of people who will be living with AD in 2020, 2030, 2040, and 2050 to predict the total annual cost of AD in future decades. Few large-scale national surveys of the monetary cost or economic burden of AD have been conducted in China, or indeed in Asia. To remedy this lack of data, we also systematically review COI studies of AD that report annual costs per patient. This will enable estimation of the proportion of the global burden of AD costs faced by China. Furthermore, it will enable comparison of the economic burden of AD in developed and developing countries.

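### Outpatients are listed by a visit in the last 3 months and their visits are counted over 3 months and annualised, so the visit-driven part of F_1_2 is biased upward against an annual headcount

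*Protocol article*

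**What the plan says.** Data collection procedure: electronic records serve to "identify elderly patients diagnosed with AD among outpatients (in the last 3 months), inpatients (in the last 12 months", and patients are also found among "those living in urban residences and rural residences with their families, and residents of nursing homes, gerocomiums, or care facilities". The look-back is thus 3 months for outpatients and 12 months for inpatients.

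Direct medical costs: the outpatient items recorded include "the number of outpatient visits in the past 3 months, and the cost of the last clinic visit in the same 3-months period". Hospital admissions are counted over 12 months.

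Total cost per patient per year: "All of the costs will be converted into the average annual cost". No factor is printed; for a 3-month count the natural one is 4.

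Per capita annual cost: F_1_2 "is the average annual cost in the outpatient group". The untreated group, which supplies F_2, is defined by the questionnaire: "Patients described as not accepting treatment are those who did not select either" outpatient or hospital costs.

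Nationwide cost due to AD: F_1_2 is multiplied by M_1_2, which is 6/7 of all treated patients. The 6/7 comes from a pilot finding that "the average annual ratio of inpatients to outpatients in different hospitals is ~1:6". The treated share itself, 10–30%, is taken from the literature (Current total number of patients with AD in China).

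**The concern.** For outpatients, the window that puts a patient on the list is also the window over which the visits are counted. Two errors follow, both upward.

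- The count is truncated at zero before it is annualised. Someone seen once a year can be listed only in the quarter of that visit, and is then booked at 4 visits a year.
- The chance of being listed rises with visit frequency, so frequent attenders are over-represented.

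A mean taken among 3-month attenders is then applied to a yearly headcount. The two would fit only if M_1_2 counted 3-month attenders, and it does not. Hospital admissions escape the problem, because their listing and counting windows both span 12 months and match the annual headcount.

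At stake is the outpatient component of the national cost, one of the study's two main results. A larger sample does not reduce this bias.

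**Working it through.** **The plan's own figure.** No visit rate or visit cost is stated, so there is none to reproduce on this point. The one design calculation does reproduce: (1.96 × 11,037 / 500)² = 1,871.8, so 1,872; dividing by 0.75 gives 2,496, about 2,500 (α = 0.05 is assumed, as none is printed). The point does not depend on it.

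**Inputs.** From the protocol: a 3-month listing window, a 3-month counting window, conversion to a year (×4 implied), M_1_2 = 6/7 of treated patients, and a treated share of 10–30%. Assumed: the visit rate, its pattern, and the share of F_1_2 that is driven by visits.

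**Step 1: Poisson visits at rate L per year.**
- Chance of being listed: 1 − exp(−L/4).
- True visits per patient with at least one visit in the year: L / (1 − exp(−L)).
- Annualised visits among listed patients: 4 × (L/4) / (1 − exp(−L/4)) = L / (1 − exp(−L/4)).

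| L | Chance listed | True | Booked | Ratio |
|---|---|---|---|---|
| 2 | 0.39 | 2.31 | 5.08 | 2.20 |
| 4 | 0.63 | 4.07 | 6.33 | 1.55 |
| 6 | 0.78 | 6.01 | 7.72 | 1.28 |
| 12 | 0.95 | 12.00 | 12.63 | 1.05 |
| 24 | 1.00 | 24.00 | 24.06 | 1.00 |

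**Step 2: rates that vary between patients** (gamma, coefficient of variation 1). The true mean becomes L + 1 and the booked mean L + 4: 3 against 6 (×2.0), 5 against 8 (×1.6) and 13 against 16 (×1.23) for L = 2, 4 and 12.

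**Step 3: regular attenders.** With a visit every k months and k above 3, the chance of listing is 3/k and a listed patient is booked at 4 a year: 3 true against 4 booked for k = 4, 2 against 4 for k = 6, 1 against 4 for k = 12. For k of 3 or less there is no error.

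**Step 4: from visits to F_1_2.** F_1_2 sums all cost types. Only visit charges, and visit travel if scaled in the same way, carry the inflation. With visit share s of the correct F_1_2 and inflation R, F_1_2 is multiplied by 1 + s(R − 1). For the 4-a-year case, measured against all treated patients including those with no visit that year, R = 6.33/4 = 1.58:
- s = 0.10: 1 + 0.10 × 0.58 = 1.06
- s = 0.30: 1.17
- s = 0.50: 1.29

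Using R = 1.55 instead gives 1.055 to 1.275. At 12 a year (R = 1.05) the effect is 0.5–2.5%.

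**Step 5: to the national total.** M_1_2/M lies between 0.10 × 6/7 = 0.086 and 0.30 × 6/7 = 0.257. If per-patient costs were alike across groups (an assumption), the total moves by 0.086 × 6% = 0.5% up to 0.257 × 29% = 7.5%.

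**Step 6: would 12-month counts on the 3-month list be enough?** No. For Poisson L = 4 the listed patients' 12-month mean is 6.33/4 + 3 = 4.58, against 4.07 for annual attenders. Truncation has gone, but over-sampling of frequent attenders remains.

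**The case against.** Several objections have force.

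- *Patients from residences, care facilities and inpatient lists can have zero visits.* True. A reader might infer that nobody in the study can have fewer than 4 annualised visits; the recruitment routes rule that out. It does not rescue F_1_2, though. A patient with neither outpatient nor hospital costs goes to F_2, and outpatient visits are asked about over 3 months, so the outpatient group has at least one visit in the window by either route.
- *The ratios concern visits, not cost.* This stands. A reader might take 2.2 or 1.55 as the overstatement of F_1_2 or of the national total. Informal and formal care, nourishment, equipment and self-bought drugs are not measured through the visit count, so neither inference is supported.
- *If most patients attend regularly at least every 3 months, nothing is lost.* Also true. No visit rate is given, so this can be neither assumed nor excluded.
- *The factor 4 is not printed, and no anchor date ties the record search to the counting window.* Correct. But both windows are given as the most recent 3 months, and all costs must be made annual. The site covariate in the cost model and the listed sensitivity analyses (prevalence, salaries, share living at home, caregiver time) do not touch selection on attendance.
- *Fieldwork from October to March means the look-back never reaches April to June.* A reader might infer a seasonal bias, but the documents give no direction or size for one.

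**Conclusion.** The point holds for the visit-driven part of F_1_2. As written, listing and counting over 3 months and then applying the result to an annual headcount biases that part upward wherever some outpatients attend irregularly or less often than every 3 months.

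The size cannot be fixed from the documents. Under assumed Poisson attendance the overstatement of visits runs from about 5% at 12 visits a year to about 120% at 2, and it is nil for regular attendance every 3 months or more often. The effect on F_1_2 is smaller, and the effect on the national total smaller again; both rest on the assumed visit share, and the second also on similar costs across groups. The conclusion also takes the implied factor of 4 and coinciding windows as the natural reading.

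**What to change.** For record-listed outpatients, extract 12-month visit dates and charges from the electronic records already in use, and put them in place of the 3-month count times 4. Then do one of two things:

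1. List outpatients over the last 12 months, as is done for inpatients.
2. Keep the 3-month list and weight each listed patient by the inverse of the chance that a 3-month window contains a visit, estimated from that patient's own 12-month visit dates. The shortcut 1/(1 − (3/4)^v) for v visits is valid only if visits fall independently across the year. A regular quarterly attender is always listed, yet the shortcut gives 1 − 0.316 = 0.684 and over-weights that patient by 1.46.

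The cost is a little more record extraction, some precision lost to weighting, and less exact 12-month recall for patients reached only by interview.

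The planned end of fieldwork was March 2016. If data collection has closed and the records cannot be reopened, report F_1_2 as the cost of 3-month attenders and add a sensitivity analysis of the national total over a stated range of visit rates and patterns.

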**Methods:**

This study planned to start in October 2015 and to finish in March 2016. It covered 30 provincial, municipal, and autonomous regions in mainland China. The sites and research centres in each region were selected randomly. The participating sites include Tier 3 hospitals, psychiatric hospitals, geriatric hospitals, nursing homes, and residences. More than 2500 patients with AD and their caregivers from all of the 81 research centres will be enrolled to fulfil the calculated sample size. The monetary costs of AD, which include direct medical costs, direct non-medical costs, and indirect costs, are being collected using the electronic medical record system and residence health system at each site; face-to-face interviews are being performed when necessary. Descriptive statistics will be used to summarise the patient characteristics and generalised linear models will be developed to calculate the costs.

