## Discussion

To the best of our knowledge, this is the first study on AD cost that encompassed nearly all of the provincial, municipal, and autonomous regions in mainland China. To complete this survey, it is crucial to prepare a thoughtful and well-designed protocol. In the study design phase, we referred to an international popular survey method and adjusted it to China’s national conditions. We also tested the protocol in a pilot study; the results suggested that this protocol can be used in China.

This protocol includes measures specific to problems that exist in China. First, China has the largest population of any country, and the varying economic development among regions [36] might result in introduction of bias. To avoid this, the study includes 30 of the 33 provincial, municipal, and autonomous regions in mainland China. This ensures that both poor and rich areas are covered to balance the gap between them because people in poor areas may have more health problems [37]. Second, in China, hospitals with physicians for patients with AD include Tier 3 general hospitals, gerontology hospitals, mental health centres, psychiatric hospitals, and other institutions such as nursing homes, gerocomiums, and care facilities [36]. Therefore, all types of institutions are included in the current investigation to ensure representation of the diversity of AD costs among hospitals and institutions. The hospitals and institutions are selected randomly to reduce the test error. Third, the target population of this survey is patients with AD. Accurate diagnosis of AD is required for calculation of the true monetary cost of the condition. AD patients diagnosed according to the NINCDS-ADRDA criteria are enrolled in the study. In particular, to ensure accuracy, the diagnosis of patients diagnosed with AD prior to the start of this study was re-confirmed. In addition, the project team comprises a group of dementia physicians, who are trained in the diagnostic processes for dementia and AD to guarantee the quality and consistency of the diagnosis. Fourth, for accurate determination of the costs associated with AD patients, electronic records systems are used to determine the costs of all treatment items. This measure guarantees the absence of error. Therefore, the current protocol facilitates determination of the cost burden of AD patients in China.

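### Costs come first from the enrolling site's records with the questionnaire as fallback, so care elsewhere may be missed, and untreated status is read from a questionnaire some patients may not complete.

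*Protocol article*

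**What the plan says.** The Abstract (Methods) says that the costs "are being collected using the electronic medical record system and residence health system at each site", and that "face-to-face interviews are being performed when necessary". Data collection procedure sets the same order: the questionnaire is administered "when the data and information could not be collected through electronic medical record or residence health systems". The Discussion goes further: "electronic records systems are used to determine the costs of all treatment items. This measure guarantees the absence of error".

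Direct medical costs sets out what is to be measured. It counts a patient's outpatient visits over 3 months and hospital admissions over 12 months, whether for AD, related symptoms or comorbidities. Neither count is restricted to the enrolling site. Total cost per patient per year then adds the direct medical, direct non-medical and indirect costs for each patient.

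The section on per capita annual cost splits patients by treatment. Those counted as not accepting treatment "are those who did not select either “outpatient service costs” or “hospitalised costs” in their questionnaire". Their mean annual cost is F_2, which Nationwide cost due to AD multiplies by M_2, the national number of untreated patients.

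**The concern.** There are two linked problems.

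- **Coverage.** The target is all of a patient's care, but the first source is one site's record. Such a record shows what that site delivered and does not show that something was delivered elsewhere. If it already holds visits and costs, nothing in the stated rule need prompt an interview. Comorbidity costs are in scope, and the listed comorbidities include stroke, cancer, diabetes and heart disease, so use of a second provider is plausible. The article describes no linkage to other providers and no completeness check.
- **Classification.** Untreated status is defined by the absence of a selection in the questionnaire, while the questionnaire is conditional on the record falling short. A patient whose outpatient or inpatient cost came from the record may therefore have made no selection and, read literally, counts as untreated.

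At stake are the per-patient annual cost and the three means (F_1_1, F_1_2 and F_2) that build the national total.

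**Working it through.** **The article's own figure.** Its only reproducible figure nearby is the sample size. With SD 11,037, allowable error 500 and two-sided alpha 0.05 (assumed; no value is printed), (1.96 × 11,037 / 500)² = 1,871.9, which rounds up to 1,872. Then 1,872 / 0.75 = 2,496, or about 2,500. Both agree with the article. Neither bears on this point, because a larger sample does not remove a measurement bias.

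**The rules side by side.**

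| Rule | Where | What it presumes |
|---|---|---|
| Record first, questionnaire if the record falls short | Abstract; Data collection procedure | Some patients may not need the questionnaire for a given item |
| Visits and admissions counted per patient | Direct medical costs | Care at every provider is known |
| Untreated = no selection in the questionnaire | Per capita annual cost | Every patient has answered those items |
| Records cover all treatment items without error | Discussion | The site's record is complete |

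The first and third rules do not fit together. The second needs information that the first does not reliably bring in.

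**Weight of F_2.** Current total number of patients with AD in China puts the treated share d at 10-30%, so M_2/M = 1 − d = 70-90%. This is a share of patients, not of cost. Because d comes from earlier reports and not from the sample, misclassification alters the means but leaves M_1 and M_2 unchanged.

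**Illustration 1: missed care.** The article gives neither the share of care used elsewhere nor the share of cost that is direct medical. Assume direct medical cost is 20-50% of the total and 10-50% of it is missed. The understatement of mean total cost is the product of the two:
- low: 0.20 × 0.10 = 2%
- high: 0.50 × 0.50 = 25%

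**Illustration 2: misplaced patients.** Let t be the treated share of the sample and m the fraction of treated patients placed in the untreated group. The share s of that group who were in fact treated is s = t·m / (t·m + 1 − t). All values of m, and the use of these values of t for the sample, are assumptions.
- t = 10%, m = 5%: 0.005 / 0.905 = 0.6%
- t = 30%, m = 30%: 0.09 / 0.79 = 11.4%
- t = 70% (assumed because many sites are hospitals), m = 5%: 0.035 / 0.335 = 10.4%
- t = 70%, m = 30%: 0.21 / 0.51 = 41.2%

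**Direction.** Missed care lowers the means. Treated patients placed in F_2 shift it by s × (their recorded mean − the mean of the truly untreated), which may raise it. The two effects can oppose each other, so the net sign for the national total is not determined.

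**The case against.** The strongest defence is that the article describes one coherent instrument in condensed form. Visits and admissions are defined per patient, so care at another provider is naturally information that the site's record could not supply, and the fallback would then apply. The definition of untreated status presumes that patients have a questionnaire, and Quality control describes it as a piloted study instrument. Self-bought medicines, nourishment, caregiver hours and salary are unlikely to sit in a hospital record, so most caregivers would be interviewed anyway. The case report form and operator manual, which are not shown, may ask about any provider.

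Much of this stands, and it rules out several stronger readings that a reader might infer:

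- **That care elsewhere is entered as zero.** The article never says so. It supports only that such care may be missed.
- **That treated patients are certainly misclassified.** This follows only if the outpatient and hospitalisation items are skipped, or filled from the site's record, when a record exists.
- **That hospitals rely on records and other settings on recall.** Residences must themselves have a health record system to be eligible, and that system is a named source.
- **That the national total is biased by a stated percentage or in a known direction.** The inputs are not in the article.

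The defence does not remove the conflict in what is printed. An interview held for caregiver time does not show that the visit and admission items were asked when the record already held some. The Discussion names records as the source for all treatment costs, which weakens the reading that the fallback was meant to capture outside care. The claim of no error is a positive statement that cannot be left to a manual.

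**Conclusion.** The point holds as a conflict between stated rules with a real risk of bias, and it should be corrected. As written, the collection order may miss care at other providers, and the untreated definition may place patients costed from the record in F_2. The statement in the Discussion that "This measure guarantees the absence of error" is unjustified.

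The size is unknown. The 2-25% understatement of total cost and the 0.6-41.2% contamination of the untreated group show what the assumed inputs would imply; they are not estimates for this study. The only figure that rests on the article alone is the 70-90% headcount weight on F_2. The conclusion assumes that the unseen case report form and manual do not already ask every patient about care at any provider. If they do, what remains is to correct the text.

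**What to change.** 1. Define treated or untreated status from either source: a patient with outpatient or inpatient care in the record or in the questionnaire is treated. The cost is a recoding rule.
2. Ask every patient or caregiver about outpatient visits and admissions at any provider within the windows already stated. Use the site's record to verify and price what it holds, and add reported care elsewhere. The cost is a few items, which can go into the interview needed for informal care, nourishment and self-bought medicines. The downside is some recall error for care at other sites.
3. Collection was planned for October 2015 to March 2016 and the article appeared in January 2017, so new items may no longer be possible. In that case, reclassify status from both sources, report the source of the cost data by setting, and state possible under-capture of outside care as a limitation.
4. Reconcile Data collection procedure with the definition of untreated patients, and delete the claim that records guarantee no error. The cost is an edit to the text.
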